## Abstract

**Background:** An urgent need exists for evidence-based dietary guidance early in life, particularly regarding protein intake. However, a significant knowledge gap exists in the effects of protein-rich foods on growth and development during early complementary feeding.

**Methods:** This is a randomized controlled trial of infant growth and gut health (primary outcomes). We directly compare the effects of dietary patterns with common protein-rich foods (meat, dairy, plant) on infant growth trajectories and gut microbiota development (monthly assessments) during early complementary feeding in both breast- and formula-fed infants. Five-month-old infants (up to *n* = 300) are randomized to a meat-, dairy-, plant-based complementary diet or a reference group (standard of care) from 5 to 12 months of age, with a 24-month follow-up assessment. Infants are matched for sex, mode of delivery and mode of feeding using stratified randomization. Growth assessments include length, weight, head circumference and body composition. Gut microbiota assessments include both 16S rRNA profiling and metagenomics sequencing. The primary analyses will evaluate the longitudinal effects of the different diets on both anthropometric measures and gut microbiota. The secondary analysis will evaluate the potential associations between gut microbiota and infant growth.

**Discussion:** Findings are expected to have significant scientific and health implications for identifying beneficial gut microbial changes and dietary patterns and for informing dietary interventions to prevent the risk of overweight and later obesity, and promote optimal health.

**Clinical Trial Registration:**
www.ClinicalTrials.gov, identifier: NCT05012930.

## Introduction

Undesired growth patterns during infancy, namely rapid weight gain or excessive weight gain relative to length, are strongly associated with childhood obesity (1, 2). Overweight and obese children have an increased risk of becoming overweight and obese adults and could experience an earlier onset of chronic diseases such as type 2 diabetes and CVD (3). Given the current obesity rates in U.S. children and adolescents (4), identifying modifiable risk factors underpinning excessive weight and adiposity gain early in life is urgently needed.

Early complementary feeding represents the progressive introduction of solid foods between 5 and 12 months of age as infants no longer rely solely on breastmilk or formula. Growth trajectories and shifts in the composition of the gut microbiota during this critical period have the potential to program long-term body weight, body composition, and disease risk, with diet exhibiting significant influence. Among the macronutrients, protein has gained great interest over the years. Multiple observational and randomized controlled trials (5–7) have evaluated protein content in liquid diet (i.e., infant formula) and most studies observed a lower-protein content in infant formula led to less weight gain and lower weight-for-length Z scores (WLZ). These findings at least partially contributed to the recommendations of reducing protein intake during complementary feeding (8). However, a significant knowledge gap exists regarding the effects of different protein-rich foods on growth during early complementary feeding.

Research of protein-rich complementary foods on growth and risk of overweight is quite limited. Several observational studies focused on the long-term effect of early protein intake, but results were inconsistent. One study in Iceland found that the intake of animal protein at 12 months (meat and dairy combined), but not plant-based protein, was associated with higher BMI at age 6. Importantly, dairy protein was also associated with higher IGF-1 (9), which is associated with a higher risk of obesity early in life (10). A larger study in the Netherlands had similar findings, and the association between animal protein and BMI did not differ between meat and dairy (11). However, another study from Germany found that dairy intake at 12 months was associated with BMI at age 7, while meat or plant was not (12). A 2019 Cochrane review on animal-source foods for growth and development in infants and young children rated the quality of the current evidence as very low overall and no firm conclusions can be drawn (13). Likewise, a 2019 systematic review by the B-24 committee concluded that there is insufficient evidence of an association between protein intake and incidence of overweight or obesity early in life (14).

Another health indicator that might link diet and growth is the gut microbiota. The role of gut microbiota in human health, including obesity risks, has been examined primarily in adults and animal models (15, 16). Emerging research suggests that early-in-life colonization plays a critical role in the establishment and maturation of gut microbiota, and disruption of the optimal microbial succession may result in long-term health impairments (17). Although gut microbiota are greatly influenced by diet, very few studies have addressed the effects of complementary foods on infant gut microbiota. Several observational studies (18) showed significant shifts of both diversity (19) and community structure of the gut microbiota during weaning and dependent on types of complementary foods consumed (20). One animal study (21) compared meat-, dairy- and plant-protein extracts and found *Ruminococcaceae* was one of the characteristic bacteria in rats fed with meat proteins. A previous study from our group in 6–9 month-old infants showed that compared with a low-protein, cereal-based complementary diet (9% energy from protein), a high-protein, meat-based diet (17% energy from protein) increased the abundance of short-chain fatty acids (SCFA)-producing *Lachnospiraceae* (22). This project will directly assess the development of gut microbiota during the transition from liquid diets (breastmilk or formula) to complementary feeding, and in response to different protein-rich foods.

Emerging research has shown that gut microbiota can directly regulate growth. One animal study (23) found that gut microbiota drives growth during the juvenile period. A landmark cohort study (24) identified bacterial species whose proportional representation defined a healthy and mature gut microbiota during the first year of life in Malawian infants. Specifically, deviation from the normal gut microbiota, such as low diversity and absence of certain species, resulted in “immature” gut microbiota and growth impairment (24). Furthermore, transplanting gut microbiota from stunted infants to germ-free mice also transmitted impaired growth phenotypes, and adding back the two major growth-discriminatory species (*Ruminococcus gnavus, Clostridium symbiosum*) ameliorated growth impairment in mice (24). *Ruminococcus* and other short-chain fatty acids (SCFA) producing strains may increase the gut SCFA content, which, in animal models, could directly promote bone growth (25). Two recent cohort studies found that disrupted maturation of the gut microbiota, as indicated by low diversity, is associated with growth failure in preterm infants (26) and slower growth in weight in Malawian infants (27). However, a recent cohort study (28) found that the abundances of SCFA producing families *Lachnospiraceae* and *Ruminococcaceae* at 4 months were associated with a higher risk of overweight at 12 months. Current findings, although limited and primarily in animal and cohort studies, suggest that gut microbiota could impact growth and risk of overweight. The project presented here will directly assess the relation of gut microbiota and infant growth longitudinally and its potential mediating effect.

### Objectives and Hypotheses

#### Goal

The goal of this randomized controlled feeding trial is to establish how infant diet with different protein-rich foods affects growth trajectories and gut microbiota development during the early complementary feeding phase.

#### Aims

The objective of this study is to determine the impact of different types of common protein-rich foods on infant growth (Aim 1) and gut microbiota (Aim 2). We also seek to identify the role of the gut microbiota in infant growth (weight, length, head circumference, adiposity), specifically, whether the gut microbiota is a mediator linking protein-rich foods and infant growth (Aim 3).

#### Hypotheses

Primary: Growth trajectories (weight, length and body composition) and gut microbiota (diversity and composition) during early complementary feeding will differ by types of protein-rich foods consumed. Specifically, meat- and plant-based diets will have a lower weight-for-length Z score and adiposity, more age-appropriate and diverse gut microbiota than dairy and the reference groups. Secondary: A more mature, diverse microbiota will be positively associated with infant growth and that diet-induced infant growth trajectories will be mediated by the gut microbiota.

## Methods

### Study Design

This is a randomized controlled feeding trial with four groups. After screening, eligible participants and their caregiver(s) will visit the Clinical & Translational Research Center (CTRC) at Children's Hospital Colorado (CHCO) to complete the baseline visit (Figure 1) at 5 months of age. After obtaining informed consent, participants will be assigned and randomized to one of the four study diets: (1) a meat-protein-predominant diet group (Meat); (2) a dairy-protein-predominant diet group (Dairy); (3) a plant-protein-predominant diet group (Plant); or (4) a reference group without intervention (Reference).

**Figure 1 F1:**
[figure not shown]
Experimental design.

The baseline visit includes consenting to study participation, a questionnaire of infant feeding and family health history, family demographics, parental weight and height, gestational weight gain, parity, maternal smoking, and other variables that could affect outcomes. Blood, urine and stool samples are collected. Urine samples are used for body composition and total energy expenditure assessments using the doubly labeled water method with procedures designed for infants. A fasting breastmilk sample is also collected at baseline. When the intervention ends at 12 months of age, participants come to Children's Hospital Colorado CTRC to complete the end of the intervention visit. During the intervention (5–12 months), monthly home visits are conducted to (1) deliver study foods to Meat, Dairy and Plant and grocery vouchers to Reference, and infant formula if formula-fed or mixed feeding; (2) complete a health and dietary questionnaire; (3) obtain length and weight measurements; (4) collect a stool sample; (5) collect 3-day diet record and the food tracking log; (6) collect a breastmilk sample if breastfeeding.

### Timeline and Milestones (in Months, Commencing March 1, 2021)

0–5 Study preparations: Manuals of operation, IRB approval, Children's Hospital Colorado Research Institute Approval and Clinicaltrials.gov registration.6–48 Enrollment of 260–300 eligible participants and complete all baseline visits.21 Completion of 50% participants in each group complete.54 All clinical procedures complete.60 Laboratory analyses of blood, urine and stool analyses, data analyses complete.

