### Participants

Participants are being recruited in the metro Denver area from households with 3–4 month-old infants via direct mailing by Colorado Department of Public Health & Environment (CDPHE) which has access to the birth registry. Up to 300 infants will be recruited (75/group) to have at least 240 completers (60/group), based on a conservative estimate of 20% attrition.

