### Follow-Up Procedures: 12-Month and 24-Month Visits

At 12 months of age (±7 days), the study participant returns to the Children's Hospital CTRC to complete their end of intervention visit. The visit includes the same procedures and sample collections as the baseline visit. The dietary intervention ends at 12 months. At the 12-month visit, caregivers are asked whether they want to consent to a 24-month follow-up visit. If so, caregivers sign another consent for the 24-month follow-up. When the participant turns 24 months, 1 year after the intervention ends, they come back to the Children's Hospital CTRC and repeat the procedures at baseline and 12 months, except for body composition and total energy expenditure assessment.

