### Power Calculation and Sample Size Justification

We hypothesize that both the gut microbiota and infant growth trajectories are dependent on types of protein-rich foods consumed. We will recruit up to 75 infants/arm and use a conservative 20% attrition which results in 60/group (total completers *n* = 240). Sample size and power justification are from the longitudinal models with feeding group as the predictor and either gut microbiota (i.e., diversity and *Ruminococcus* abundance) and growth (i.e., linear growth parameter LAZ, overweight parameter WLZ and growth velocity using the WHO 0–24 months standards) as the outcomes. We completed power simulations (1,000 replicates) using a linear mixed-effects model (LME) with random effects by subject. For the simulations, we used parameter estimates (e.g., fixed and random effects) from our randomized pilot study on the gut microbiota and infant growth trajectories after receiving meat- or dairy-based complementary diet (30). We simulated a variety of scenarios assuming that Plant had microbiota and growth outcomes that were either worse than Dairy, between Dairy and Meat, or the same as Meat. *To be conservative, we estimated power after increasing the within-group variability by 50%*. The power is above 80% in all simulated scenarios (80–90%) where the effect size was simulated to be at least 50% of that observed in our pilot study (30). The power of most simulation scenarios was below 80% when the effect size was 25% of that observed in the pilot study (30).

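### The milestone list conflicts with the visit schedule (last 24-month visit at month 67, clinical procedures to end at month 54), and its enrolment floor of 260 gives 208 completers, not 240

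*Protocol article*

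**What the plan says.** **Calendar.** Timeline and Milestones sets "6–48 Enrollment of 260–300 eligible participants and complete all baseline visits.21 Completion of 50% participants in each group complete.54 All clinical procedures complete", and then "60 Laboratory analyses of blood, urine and stool analyses, data analyses complete", all in months from 1 March 2021. The Enrollment and Randomization sections also describe recruitment over four years, so month 48 is not an isolated figure. The interim milestone within that list is "21 Completion of 50% participants in each group complete".

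**Visits.** Under Study Design, baseline is at 5 months of age. Under Follow-Up Procedures: 12-Month and 24-Month Visits, the intervention ends with a visit at 12 months of age (±7 days). Then: "When the participant turns 24 months, 1 year after the intervention ends, they come back to the" research centre, if the caregiver signs a second consent. Primary Outcomes lists anthropometry and a stool sample at 24 months.

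**Sample size.** Participants states: "Up to 300 infants will be recruited (75/group) to have at least 240 completers (60/group), based on a conservative estimate of 20% attrition". Power Calculation and Sample Size Justification uses the same 60 per group and reports: "The power is above 80% in all simulated scenarios (80–90%) where the effect size was simulated to be at least 50" per cent of the pilot effect.

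**The concern.** The milestones, the visit ages and the sample size are each stated plainly, but they do not fit together. The last infants allowed to enrol reach 24 months of age well after the date on which clinical work is to stop, and even after the date on which analysis is to be finished. If those dates hold, 24-month data are lost according to enrolment date. The 20% attrition allowance is not described as covering such a loss.

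The lower end of the enrolment range is a separate matter. At 20% attrition, 300 is exactly the number needed for 240 completers, and it is also the ceiling. A milestone that is met at 260 therefore accepts a sample which, at the plan's own attrition rate, is smaller than the one its power rests on.

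**Working it through.** **1. Calendar.** Inputs: last baseline at month 48, baseline age 5 months, visits at 12 and 24 months of age.

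- Time from baseline: 12 − 5 = 7 months; 24 − 5 = 19 months.
- Last 12-month visit: 48 + 7 = month 55, one month after month 54. The ±7-day window does not close that gap, and seven days of urine collection follow the visit.
- Last 24-month visit: 48 + 19 = month 67, which is 13 months after month 54 and 7 months after month 60.
- Latest baseline that allows a 24-month visit by month 54: 54 − 19 = month 35. By month 60: 60 − 19 = month 41.

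**2. How many infants this touches.** The article gives no accrual rate, so two assumed patterns are shown for 300 infants enrolled over months 6–48.

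| Accrual pattern (assumed) | Enrolled after month 35 | Enrolled after month 41 |
|---|---|---|
| Even over 42 months | 13/42 = 31%, about 93 | 7/42 = 17%, about 50 |
| 150 by month 14, the other 150 evenly over months 14–48 | 150 × 13/34 ≈ 57, 19% | 150 × 7/34 ≈ 31, 10% |

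The second pattern comes from the month-21 milestone, if complete means having had the 12-month visit: 21 − 7 = month 14. It needs 150/8 ≈ 19 infants a month at first, against 300/42 ≈ 7 a month under even accrual.

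**3. Completers.**

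- The plan's own figure reproduces: 300 × (1 − 0.20) = 240, and 75 × 0.80 = 60 per group.
- At the floor: 260 × 0.80 = 208, or 52 per group, which is 240 − 208 = 32 short.
- Attrition at which 260 still gives 240: 1 − 240/260 = 7.7%.

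**4. Power at 52 per group.** The simulation inputs come from a pilot study and are not given, so the simulations cannot be repeated. As an approximation, take the stated power to apply at 60 per group and scale the non-centrality by √(52/60) = 0.931 (two-sided 5%).

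- From 80%: (1.960 + 0.842) × 0.931 − 1.960 = 0.65, giving about 74%.
- From 90%: (1.960 + 1.282) × 0.931 − 1.960 = 1.06, giving about 85%.
- A four-group F test (3 df) scaled in the same way gives 73% and 85%.

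**The case against.** **The 24-month visit is not central to the analysis.** The hypotheses concern the complementary-feeding period, the intervention stops at 12 months, the 24-month visit needs its own consent, and the Statistical Approach sets no 24-month contrast. Month 54 may have been meant for the intervention phase, where the overrun is one month and affects only the last infants enrolled. This stands as a limit on the consequences. It does not remove the conflict: the milestone covers all clinical procedures, the 12-month visits miss it too, and 24-month growth and stool are listed under primary outcomes.

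**No data need be lost.** A reader might infer that the design cannot be delivered, or that late enrolees will certainly lack 24-month data. The article does not say so. The milestone itself may be what is wrong, and moving it would lose nothing. The percentages above apply only if month 54 or month 60 is enforced.

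**The month-21 milestone.** It is tempting to call this an error, because even accrual would have only 8/42 = 19% of infants enrolled by month 14. But even accrual is an assumption. Heavy early enrolment is demanding yet compatible with an end by month 48, and the line does not say what is completed. No error is shown.

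**208 is a worst case.** It pairs the lowest enrolment with an attrition rate the plan calls conservative, and Compliance Monitoring reports low drop-out in the team's earlier infant trials. With 260 enrolled, the same scaling turns 80% into about 79% at 10% attrition and 77% at 15%. The simulations already inflated within-group variability by 50%, and a mixed model also uses visits from infants who later leave. All of this stands, so 74–85% should not be read as the trial's power. What remains is that nothing in the article ties stopping at 260 to lower attrition.

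**Conclusion.** The concern holds in two limited parts and should be fixed.

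1. The closing milestones contradict the visit schedule by one month for the 12-month visit and 13 months for the 24-month visit. This follows from the article's own figures with no further assumption. If month 54 is binding, roughly 19% to 31% of infants could not have a 24-month visit, depending on the assumed accrual pattern.
2. The enrolment floor of 260 does not support 240 completers at the stated 20% attrition; it gives 208. The possible loss of power is modest, about 5 to 6 percentage points by approximate scaling, and arises only if floor enrolment and 20% attrition occur together. It would take the weakest scenarios, stated at about 80%, below that level.

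Neither part touches the randomisation, the models or the 5–12 month comparison beyond these points.

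**What to change.** **Milestones.** Restate the end of clinical procedures as month 55 for the intervention phase and month 67 for the 24-month visits, and move the analysis milestone to match. Keeping the present six-month interval gives month 61 for the intervention-phase analyses and 67 + 6 = month 73 for the 24-month analyses. If the study cannot run that long, define the 24-month set as infants enrolled by month 35, treat later infants as administratively censored, and state the expected size. Before dropout and refusal of the second consent, that is about 207 of 300 under even accrual, or about 243 under the front-loaded pattern. Check the month-21 milestone against actual accrual at the same time and say what is meant by complete.

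**Sample size.** State that recruitment continues, up to 300, until 240 infants complete. Because completion is known only seven months after baseline, a decision to stop early has to rest on observed attrition to date. Alternatively, keep 260–300, rerun the simulations with the pilot inputs at 52 per group, and report that power beside the present figure. The scaled values above indicate the size to expect and should not be printed as the result.

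**Cost.** The text changes are small. The real choice is between a longer follow-up period and a smaller stated 24-month sample, and between a firm completer target and a less favourable power figure at the floor.

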### Participants

Participants are being recruited in the metro Denver area from households with 3–4 month-old infants via direct mailing by Colorado Department of Public Health & Environment (CDPHE) which has access to the birth registry. Up to 300 infants will be recruited (75/group) to have at least 240 completers (60/group), based on a conservative estimate of 20% attrition.

#### Inclusion Criteria

Full term (gestational age equal or over 37 weeks); generally healthy without conditions that would affect protein metabolism or growth; no previous complementary food exposure; no prior exposure of antibiotics during delivery or after birth; able to consume study foods; No known food allergies.

#### Exclusion Criteria

Pre-term or small-for-gestational age infants; Infants having conditions that would affect normal growth; Infants having had complementary foods prior to the start of the study; not willing to feed the complementary foods provided; antibiotics exposure during delivery or from birth to 5 months of life; multiple births.

### Ethical Approval

Ethical approval for this clinical trial was obtained through the Colorado Multiple Institutional Review Board (COMIRB) (COMIRB 20-2232). COMIRB conducts the initial and annual reviews of the trial, monitoring enrollment and retention, protocol deviations, and any reported adverse effects as a result of the study. All participants are provided with a copy of the signed informed consent. This protocol is registered at ClinicalTrials.gov NCT05012930.

